### Research Ethics and Approval

Ethical approval for the protocol has been obtained from the Health Research Ethics Committee at Stellenbosch University (reference number: N16/05/063). The Standard Protocol Items: Recommendations for Interventional Trials (SPIRIT) were used in designing the study and writing of the protocol. A checklist and populated checklist have been provided as per the recommendations. The trial has been registered with the ISRCTN registry (ISRCTN17244156). Should the intervention prove successful, the game will be made available to all participants. This would, however, require the participant to have access to a suitable device as providing participants with tablet computers would not be feasible.

### Setting

The RCT will be conducted in the Saldanha Bay Municipal (SBM) area in the Western Cape province of South Africa. Saldanha Bay is the largest natural port in Africa, most of the economic activity in the area is related to fishing, agriculture, and iron exports. There is, however, significant income inequality and an unemployment rate of 17% [30]. FARR has previously conducted a prevalence study in this area, where a prevalence rate of FASD of 64.2 per 1000 was found [31]. FARR subsequently implemented a comprehensive prevention and awareness program between 2013 and 2016 and is currently running an awareness program in the SBM area.

Although the aim of the intervention is to develop cognitive training for children with FASD, it is not possible to identify and diagnose a large group of children with FASD within the study’s timeframe. The intervention will thus be evaluated using children who were exposed to alcohol during pregnancy regardless of whether they have received a diagnosis of FASD. To screen for alcohol exposure, we will conduct in-depth interviews with mothers of children who attend Early Childhood Development (ECD) centers in the SBM area.

### Eligibility Criteria

#### Inclusion Criteria

Children aged between 4 and 6 years will be eligible for inclusion. Children must reside in the SBM area and attend or be enrolled in an ECD center.

#### Exclusion Criteria

Children with a physical disability that will hamper their interaction with the program will be excluded, for example, severe eyesight problems.

### Intervention

The efficacy of cognitive training is influenced by the time spent interacting with the program and the difficulty of the tasks presented, especially in terms of whether skills that are not directly trained will improve [18]. In the first step, the specific processes to be targeted were identified using the available literature. In consultation with a software developer, the basic interface and game mechanics were designed, focusing on an intuitive interface and game mechanics that will allow the same interaction to be used with all tasks. In the alpha (initial) version, it is possible to select different tasks to ensure data can be gathered for all stages and tasks. Data that are logged will include the date and time of the play session, the response time per item, and whether the correct response was selected for each item.

The theoretical basis for the game design involves 2 different definitions of *scaffolding* in 2 different contexts. The first refers to work on childhood development and cognitive development. In this context, scaffolding refers to the support of cognitive development by reducing a complex problem to subproblems, and by solving the subproblems, the ability to solve the complex problem is gained [32]. The game was developed to incrementally increase the demands on various cognitive abilities, with continued successes on one level of difficulty eventually enabling success on a higher level of difficulty.

The second context of scaffolding refers to neuroplastic scaffolding. This term is generally used in connection with age-related cognitive decline [33], but as the target population of this intervention frequently suffers from structural brain abnormalities [2], the same concept of neuroplastic scaffolding should still apply. It refers to compensatory neural activity aimed at supporting damaged, inefficient, or poorly functioning cognitive functions. Scaffolding happens through recruitment of additional prefrontal cortex activity, neurogenesis (formation of new neuronal connections), and distributing cognitive processing over various brain structures. This theory supports the hypothesis that practice and training can enhance the process of scaffolding [34]. This was the driving principle behind the conceptualization and design of the game.

To try and ensure long-term engagement with the game, meta-game elements have been added to the game in the form of a progress bar and animations that only appear once you have completed a set number of tasks. There will be no external rewards or incentives for playing. This is intentional as a key design consideration is that it should be fitting for context where no external rewards would be available. Tasks were designed to require effortful use of inhibitory control, cognitive planning, set shifting, and working memory for completion. The tasks have been designed in such a way that regardless of which function is being targeted, the interface and interaction with the participant does not change. If the interaction remains the same, it is easier to switch seamlessly between stages to maintain optimum difficulty.

The game we have designed (1) is easy to use regardless of computer literacy, (2) logs performance on various metrics (response times and error rates), (3) has continuously adaptive difficulty levels to maintain a suitable level of challenge, and (4) will be open access (free to distribute). Before making the intervention available, it is necessary to test whether it does in fact have an impact on cognitive development.

An alpha version of the program was piloted on a sample of normally developing children to ensure that the tasks escalate in difficulty. This provided an opportunity to ensure that the timing of visual stimuli is age appropriate for the proposed sample’s age. The pilot also provided normative data on participant performance to guide further development of the program.

#### Control Condition

Children in the control group will not be receiving any intervention. They will be assessed at the start of the study and there will be no further interaction with project staff or community workers until the intervention has run its course and they receive the follow-up assessment.

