### Recruitment

Trained community workers will contact mothers through the ECD centers. They will obtain informed consent to conduct a maternal interview and to include their child in the study in one of the 3 groups. The interviews will include demographic questions and information on alcohol use during pregnancy. The interview questionnaire has been used extensively in prevalence studies in South Africa to identify whether children were exposed to alcohol during pregnancy [3,31-33]. The interview will indicate if a mother consumed alcohol during pregnancy, and it will give an indication of the amount of alcohol consumed. If a child was exposed to more than 3 units of alcohol in 1 drinking session, they will be classified as *alcohol exposed*. This is in line with the latest FASD diagnostic guidelines [2].

As alcohol-exposed children are identified, they will be allocated to the intervention or control group using block randomization with a block size of 8. The randomization will be done by the primary investigator using assigned study numbers to blind them to the participants’ identity. Once a block has been filled, the 4 participants allocated to the intervention will start the intervention. The normative group will be recruited from children not exposed to alcohol during pregnancy on the basis of the maternal interviews using random number tables. A list of study numbers will be created and entries in the list will be selected based on the tables [35]. The primary investigator will be blind to participants’ identities during this operation.

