### Study Procedures

Alcohol-exposed children, as assessed by maternal interviews, will be randomized into an intervention or a control group with 40 participants in each group, using block randomization. The maternal interview will contain questions regarding alcohol use just before and during pregnancy, including the number of standard units of alcohol consumed, with 3 standard units being the threshold for determining alcohol exposure. A group of 40 unexposed children will be randomized in a group to provide normative data using individual randomization. An overview of the study design is shown in Figure 1. As the participants are drawn from a low-SES and resource-poor environment, the performance of the normative group will serve as a more suitable gauge of cognitive development in the participants’ specific contexts. This will enable us to better interpret the results of the neurodevelopmental assessments.

The SPIRIT schematic is shown in Table 1. Baseline assessments examining cognitive function will be conducted with all 3 groups. The intervention group will then play the FARR game twice a week for 6 months (40 play sessions in total). Post intervention, all 3 groups will receive follow-up cognitive assessments. Data gathered by the game will also be collected from the intervention group. All participants will start the intervention at the same level of difficulty. They will be given the opportunity to play the game during hour-long sessions facilitated by community workers. Play will, however, be self-directed; participants will be encouraged to play but will be allowed to stop at any time during a session. As participants log into the devices, they will be able to continue at the difficulty level they had previously reached.

There are 4 different stages in the game of increased complexity. After 10 trials in a stage, a participant automatically moves on to the next for 10 trials. After the fourth stage, participants start at the first stage again. The difficulty of each stage varies independently based on a participant’s performance. Getting 8 or more correct increases difficulty, getting fewer than 4 correct decreases difficulty, and otherwise the difficulty remains the same.

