### Data Analysis

For the primary hypothesis, the postintervention scaled scores of the intervention group will be compared with those of the control group. This will be done using a MANOVA with group membership as the predictor variable and the scaled scores of the 5 NEPSY-II domains (see Table 1) as outcome variables. Discriminant analysis will be done on the outcome of the MANOVA with the domain scores as predictor variables and group membership as outcome variables.

During further analysis, the baseline NEPSY-II scaled scores of the intervention and control groups will be pooled and compared with the scores of the normative group. This will also be done using a MANOVA with group membership as the predictor variable and the scaled scores of the 5 NEPSY-II domains (see Table 1) as outcome variables. Discriminant analysis will again be done on the outcome of the MANOVA with the domain scores as outcome and group membership as predictor variables.

Postintervention NEPSY-II scaled scores (see Table 1) of the intervention, control, and normative groups will be compared using a MANOVA. Group membership will be the predictor variable, and domain scores will be the outcome variables. Discriminant analysis will be conducted with the domain scores as outcome variables and group membership as predictor variables.

Difference scores between baseline and postintervention assessments will be calculated for all participants. These scores will be compared using a MANOVA with group membership as the predictor variable and changes in domain scores (see Table 1) as outcome variables. Discriminant analysis will be done on the results with changes in domain scores as outcome and group membership as predictor variables.

For the secondary hypothesis, the improvement in game performance will be quantified as how many difficulty levels a participant has successfully completed in each of the 3 different stages of the game. This will then be correlated with performance in the NEPSY-II domain scores in a covariance matrix using the Pearson correlation coefficient. A separate analysis will be done including only 6-year-old children using the additional domains tested (see Table 1).

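### Unequal contact between the randomised arms creates a risk of differential loss, and the primary MANOVA of follow-up scores on group alone gives no protection if loss is related to score

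*Protocol article*

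**What the plan says.** The protocol article treats the two randomised arms differently between assessments. Under Control Condition, control children are assessed at the start and then "there will be no further interaction with project staff or community workers until the intervention has run its course". Under Study Procedures, "The intervention group will then play the FARR game twice a week for 6 months (40 play sessions in total"), and of these children it says: "They will be given the opportunity to play the game during hour-long sessions facilitated by community workers". The same section plans one later assessment for everyone: "Post intervention, all 3 groups will receive follow-up cognitive assessments".

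Under Data Analysis the primary comparison is fixed: "For the primary hypothesis, the postintervention scaled scores of the intervention group will be compared with those of the control group". The method is a MANOVA with group as the only named predictor and five NEPSY-II scores as outcomes. (The text calls these domains and points to Table 1; the five subtests given at all ages are in Table 2.) Baseline scores are collected in all groups. They enter a baseline comparison of exposed with unexposed children and a MANOVA of difference scores, but not the primary test. The article states no expected loss rate, overall or by arm.

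**The concern.** In the intervention arm, a move, a change of centre or a wish to withdraw would come to a community worker's notice within days. In the control arm, as described, it might surface only when the follow-up assessment falls due. The arms could therefore keep different fractions of their children, or different kinds of children.

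If the children who are lost differ in score from those who stay, the comparison of follow-up means is no longer the randomised one. If low scorers are lost mainly from the control arm, the remaining controls look better and a working game looks ineffective. If they are lost mainly from the intervention arm, the error runs the other way. The Discussion says the results will guide whether the programme is kept, redesigned or replaced, so a bias that is large relative to a small planned effect matters.

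The stated analysis gives no defence. A MANOVA needs the full set of outcomes from each child, so a child without follow-up scores contributes nothing, even though that child's baseline scores are on file and could show how the lost children differ.

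**Working it through.** **Inputs from the protocol article.** 40 children per randomised arm (Study Procedures); planned effect d=0.2 (Sample Size); five outcomes, group the only named predictor (Data Analysis). The article has no loss figure to reproduce. Its power of 0.79 is not at issue here.

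**Assumed inputs.** Loss by arm, and how far lost children differ from the others. None of these comes from the documents.

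**Step 1. Shift in one arm.** Let a fraction p be lost, and let lost children lie g SD below the arm average μ. From μ = (1 − p) × (mean of stayers) + p × (μ − g), the mean of stayers is μ + g × p/(1 − p).

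**Step 2. Bias in the comparison.** The control arm is inflated relative to the intervention arm by g × [pC/(1 − pC) − pI/(1 − pI)].

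| Loss, control v intervention | g | Bias against the intervention | Share of d=0.2 |
|---|---|---|---|
| 20% v 5% (8 v 2 of 40) | 0.5 | 0.5 × (0.250 − 0.053) = 0.099 SD | 49% |
| 20% v 5% | 0.3 | 0.3 × (0.250 − 0.053) = 0.059 SD | 30% |
| 25% v 5% (10 v 2 of 40) | 0.5 | 0.5 × (0.333 − 0.053) = 0.140 SD | 70% |
| any | 0 | 0 | 0% |

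The definition of g matters. If 0.5 SD is the gap between lost and retained children, the first row becomes 0.5 × (0.20 − 0.05) = 0.075 SD, or 38% of d=0.2. If the two loss rates are exchanged between the arms, each bias keeps its size and changes sign.

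**Step 3. Simulation.** A two-group MANOVA on children with complete follow-up: five outcomes, intercorrelation 0.4, 40 per arm, no treatment effect, 4,000 runs per cell. Here r is the assumed correlation between loss and score, with lower scorers lost. Each cell gives bias in SD (negative = against the intervention), then type I error at a nominal 0.05.

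| Loss, intervention / control | r=0 | r=0.3 | r=0.5 |
|---|---|---|---|
| 10% / 10% | −0.003; 0.046 | 0.002; 0.050 | 0.000; 0.052 |
| 5% / 20% | 0.002; 0.047 | −0.068; 0.059 | −0.122; 0.070 |
| 10% / 30% | −0.001; 0.049 | −0.092; 0.061 | −0.156; 0.087 |
| 5% / 30% | 0.005; 0.050 | −0.115; 0.071 | −0.190; 0.105 |

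The simulation error on a type I rate of 0.05 is √(0.05 × 0.95/4000) = 0.003, so the r=0 column and the 10%/10% row show no meaningful departure from 0.05. Unequal loss alone does no harm to validity, and equal loss by the same mechanism cancels. Bias appears only when loss is both unequal and related to score.

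**The case against.** The strongest reply is that unequal contact is not unequal retention. Every child comes from the same small area ("Children must reside in the SBM area and attend or be enrolled in an ECD center"), and families are reached by one route: "Trained community workers will contact mothers through the ECD centers". Follow-up is planned for all three groups. Learning of a move sooner does not by itself produce a follow-up score. Forty sessions without external reward could even make loss higher in the intervention arm. This stands. It rules out saying that loss will probably be unequal, that retention differs by design, or that any bias has a known direction. It leaves a risk.

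Second, a reader might infer that the control sentence forbids tracing families. It does not say so. It describes control children having no interaction with project workers; it does not mention caregivers and does not stop a centre from reporting that a child has left. The sentence as worded provides for no contact, and it would be better to say outright that caregiver tracing is allowed.

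Third, a reader might infer that the plan has adopted a complete-case analysis set. The article states no analysis set and no missing-data rule, and an article may leave both to fuller documents. The point therefore rests on what is stated: the method, the follow-up scores and the single predictor. A MANOVA needs a complete outcome vector, and this one does not use baseline.

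Finally, this is a feasibility trial, and an untreated control group is a legitimate choice. That is accepted. Neither change below alters the control condition as a treatment.

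**Conclusion.** The concern holds as a risk, together with an avoidable weakness in the primary method. Contact differs between the arms by plan. Whether retention will differ, by how much and in which direction cannot be read from the documents.

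If loss is both unequal and related to score, the planned primary MANOVA passes the bias straight into the result. Under the assumed losses of 20% to 25% v 5% and gaps of 0.3 to 0.5 SD from the arm average, the bias is 0.059 to 0.140 SD, or 30% to 70% of d=0.2. In the simulated cells with 5% v 20% to 30% loss and r of 0.3 to 0.5, it is 0.07 to 0.19 SD, with type I error of 0.059 to 0.105. The top of that range needs both the heaviest loss and the strongest link to score.

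The tempting stronger reading, that unequal contact or unequal loss alone biases the comparison, is not supported: with loss unrelated to score the bias is zero and type I error stays at 0.047 to 0.050. The changes are still worth making, because they are cheap and the first improves the analysis whatever the loss turns out to be.

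**What to change.** **1. Primary analysis.** Replace the MANOVA of follow-up scores with a likelihood-based repeated-measures model on the baseline and follow-up scores of the five subtests. Include every randomised child with at least one score, in the allocated group, and test the difference between intervention and control at follow-up jointly over the subtests. This protects against loss that the observed scores can explain, including the baseline scores of lost children. It does not protect against loss that depends on the unseen follow-up score itself, and the text should say so. Cost: one paragraph, no new data. The Sample Size section already describes power for a repeated-measures analysis. The change should be dated and made before follow-up scores are examined by group.

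**2. Contact and recall.** Reword the Control Condition section so that controls receive no game or training, but caregivers in all three groups have the same brief checks of contact details by the existing community workers (for example every 2 months). Recall every randomised child at the same interval after baseline, whatever number of sessions was played and whether or not the child is still at the same centre. Report retention by arm. Cost: a few calls or visits per family. The small downside is that control families are no longer entirely without contact, but that contact is with the caregiver only and equal across groups. The article reports that the intervention has started for some participants, so for them the checks would cover only the remaining follow-up.

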### Recruitment

Trained community workers will contact mothers through the ECD centers. They will obtain informed consent to conduct a maternal interview and to include their child in the study in one of the 3 groups. The interviews will include demographic questions and information on alcohol use during pregnancy. The interview questionnaire has been used extensively in prevalence studies in South Africa to identify whether children were exposed to alcohol during pregnancy [3,31-33]. The interview will indicate if a mother consumed alcohol during pregnancy, and it will give an indication of the amount of alcohol consumed. If a child was exposed to more than 3 units of alcohol in 1 drinking session, they will be classified as *alcohol exposed*. This is in line with the latest FASD diagnostic guidelines [2].

As alcohol-exposed children are identified, they will be allocated to the intervention or control group using block randomization with a block size of 8. The randomization will be done by the primary investigator using assigned study numbers to blind them to the participants’ identity. Once a block has been filled, the 4 participants allocated to the intervention will start the intervention. The normative group will be recruited from children not exposed to alcohol during pregnancy on the basis of the maternal interviews using random number tables. A list of study numbers will be created and entries in the list will be selected based on the tables [35]. The primary investigator will be blind to participants’ identities during this operation.

### Data Collection

The maternal interview will be conducted by community workers. They have extensive experience in conducting this particular interview as they interviewed mothers during previous prevalence studies using the same tool. Any additional community workers required will be trained by the primary investigator. After the training, they will conduct mock interviews with their fellow community workers.

The neurodevelopmental assessments will be conducted by a psychometrist with experience in assessing by using the NEuroPSYchological Assessment, Second Edition (NEPSY-II). The psychometrist will also have extensive experience working with children exposed to alcohol during pregnancy and have participated in FASD prevalence studies.

The intervention will be overseen by trained community workers. They will be trained on how the game should be played and instructed on how they should interact with the children after they have mastered playing the game on their own. The community workers will also be trained on how to copy and secure the game logs kept on the tablet computers.

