**Assessments**					
	NEPSY-II^c^ psychometric assessment	—	X	—	X
	Data logged by FARR game	—	—	—	X

^a^Not applicable.

^b^FARR: Foundation for Alcohol Related Research.

^c^NEPSY-II: NEuroPSYchological Assessment, Second Edition.

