### Measures

The primary outcome is EF, as measured using the NEPSY-II psychometric assessment score. The secondary outcomes are (1) game performance, as measured in the game log files, (2) reaction time, and (3) increase in the level of difficulty of the task.

Additional demographic data will be gathered during the recruitment process. In addition to alcohol use, data will be gathered on age, gravidity, parity, years of schooling, and household income.

All participants will be evaluated using a selection of subtests of the NEPSY-II that measure executive functioning and working memory. Cognitive function, focusing on EFs, will be measured using the NEPSY-II [36]. The NEPSY-II is a compendium of tests based on the Luria theoretical approach to neurological assessment. It is individually administered and has been shown to be successful in diagnosing a range of childhood disorders. The subtests of this test can also be selected based on the specific domains to be tested [37].

Scores obtained on the subtests of the NEPSY-II are compared with the scores of a normative group based on age. The normative group of the NEPSY-II was selected to closely match the US population between 3 and 16 years of age [38]. This group will differ significantly from the populations of interest in this study; however, the NEPSY-II is relatively insensitive to language and culture differences. Although the results need to be interpreted cautiously, the test remains clinically useful [39]. Insensitivity to language is an important feature as the study sample will be drawn from a predominantly Afrikaans-speaking community, which could affect test performance [40].

In the standardization of the NEPSY-II, subtests showed adequate-to-high internal validity. There was no significant practice effect with re-administration of the test in a short space of time (around 3 weeks), supporting its use for both the pre- and postintervention assessments in this study [41]. Inter-rater agreement was high on both the objectively and more subjectively scored test, and the reliability of subtests remained stable [38]. The inclusion of the third group of children not exposed to alcohol in pregnancy will help guide the interpretation of results.

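### The protocol plans blinding only for the investigator who randomises; it plans no masking of the psychometrist who measures the primary outcome at follow-up against an open, untreated control

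*Protocol article*

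**What the plan says.** Blinding appears twice in the protocol article, both times in Recruitment and both times about the primary investigator. For the alcohol-exposed children: "The randomization will be done by the primary investigator using assigned study numbers to blind them to the participants’ identity". For the selection of the normative group: "The primary investigator will be blind to participants’ identities during this operation".

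Data Collection covers outcome measurement: "The neurodevelopmental assessments will be conducted by a psychometrist with experience in assessing by using the NEuroPSYchological Assessment". It adds that this person will have extensive experience with alcohol-exposed children and of FASD prevalence studies. It does not say whether this person knows a child's group.

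Four other parts of the protocol bear on the point:

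- **Control Condition:** "Children in the control group will not be receiving any intervention", and "there will be no further interaction with project staff or community workers until the intervention has run its course".
- **Study Procedures:** intervention children attend 40 play sessions over 6 months, facilitated by community workers.
- **Measures:** the primary outcome is executive function on the NEPSY-II, which is individually administered. On its scoring: "Inter-rater agreement was high on both the objectively and more subjectively scored test".
- **Data Analysis:** the primary hypothesis is tested by a MANOVA of postintervention scaled scores, intervention against control.

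**The concern.** Blinding the investigator to identities while allocating protects the allocation. It does nothing for outcome measurement 6 months later. The outcome depends on one adult testing one young child, and the protocol accepts that some of the scoring involves judgement. An assessor who knows which children have played the game may prompt, allow time or score differently without intending to, most plausibly in favour of the trained group.

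Such a shift would differ between the arms. Because the primary comparison uses postintervention scores only, it would pass straight into the treatment estimate, and no planned analysis could separate it from a real effect. The trial is sized for a small effect (d = 0.2, Sample Size), so even a modest shift is large relative to what the trial seeks to detect.

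The same knowledge could affect other comparisons. A psychometrist who knows exposure status might test or score exposed and normative children differently.

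**Working it through.** **Step 1. Who is blinded, to what, and when**

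| Role | Task | Blinding planned |
|---|---|---|
| Primary investigator | Randomises exposed children | Yes, to identity |
| Primary investigator | Samples the normative group | Yes, to identity |
| Psychometrist | NEPSY-II at baseline and follow-up | None stated |
| Community workers | Run play sessions, secure game logs | Not possible |

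The article gives no figure for assessor bias, so there is no planned number to reproduce. The rest shows what a shift would do if there were one.

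**Step 2. Inputs**

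- n = 40 per arm (Study Procedures).
- Significance level 0.05 (Sample Size); two-sided is assumed.
- True effect: none.
- Assessor shift b, in SD units: assumed, shown over the range 0.1 to 0.3. The value 0.2 equals the planned d.
- Five outcomes, as in Data Analysis and the all-ages rows of Table 2.
- Common correlation r between outcomes: assumed, 0.3 or 0.5.

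**Step 3. One score, two-sample t test**

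The noncentrality is b × √(n/2) = b × √20, with 78 degrees of freedom and critical value 1.991. For b = 0.2 it is 0.2 × 4.472 = 0.894. The chance of rejecting in favour of the intervention is 0.141 and in the other direction 0.002, in total 0.143.

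**Step 4. Five scores, Hotelling T² (the two-group MANOVA)**

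With the same shift on every score, D² = 5b²/(1 + 4r) and the noncentrality is (n/2) × D² = 20 × D². The reference distribution is F with 5 and 74 degrees of freedom, critical value 2.338. For b = 0.2:

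- r = 0.3: D² = 0.20/2.2 = 0.0909, noncentrality 1.818, rejection probability 0.138.
- r = 0.5: D² = 0.20/3.0 = 0.0667, noncentrality 1.333, rejection probability 0.112.

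**Step 5. False-positive rate (nominal 5%)**

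| Assumed shift | One score | Five scores, r = 0.3 | Five scores, r = 0.5 |
|---|---|---|---|
| 0.1 SD | 7.3% | 6.9% | 6.4% |
| 0.2 SD | 14.3% | 13.8% | 11.2% |
| 0.3 SD | 26.3% | 27.8% | 20.8% |

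At d = 0.2 the power of the two-arm comparison on one score is also 14.3%, because the calculation is the same. A shift of that size and the target effect could not be told apart.

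**The case against.** The strongest reply is that silence is not a statement. The article condenses a fuller protocol, says SPIRIT was followed and mentions a populated checklist that is not shown. It separates the roles: the psychometrist assesses, while community workers run the sessions and handle the logs. Nowhere is the psychometrist said to attend sessions, see logs or receive the allocation, and study numbers are already in use. This part stands. A reader might infer that the psychometrist is unmasked, and the documents do not say so. What can be said is that no masking is planned in the text. Who is masked is a design feature, and the article does discuss blinding, only for a different role. Separate roles also do not stop a child, parent or teacher from mentioning the game.

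A second reply points to the high inter-rater agreement cited in Measures. Agreement between raters shows consistent scoring. It does not show that one rater who knows the group is unaffected by it. It is fair, however, that the article does not say which of the five all-ages subtests, if any, are the more subjectively scored ones.

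A third concerns baseline. Table 1 puts the first NEPSY-II and allocation in the same column, and Study Procedures describes randomisation before baseline testing, so a reader might infer that children were tested at baseline with group known. A shared column does not fix the order within it, and narrative order is not a stated sequence. Baseline scores also do not enter the primary test. They matter for the change-score analysis and for the baseline comparison of exposed with normative children.

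Finally, the no-treatment comparator is a choice made for a feasibility trial, and the Discussion leaves a control group receiving some intervention to later trials. Assessor masking would not remove attention or expectation effects in the children. It would remove one separate source of bias.

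**Conclusion.** The point holds as a design weakness at follow-up. Carried out as written, the trial measures an individually administered and partly judgement-based primary outcome, against an open and untreated control, with no planned masking of the assessor.

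The size is conditional. If group knowledge shifted scores by 0.2 SD and there were no true effect, the false-positive rate would be about 14% on one score and about 11% to 14% for the five-outcome test. These figures rest on an assumed shift, an equal shift on every outcome, an assumed common correlation and a two-sided 5% test. They show what a bias would do, not that one is present or likely. The point does not extend to a claim that the psychometrist knows the groups, or that baseline testing was compromised.

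**What to change.** For the postintervention round, keep the same psychometrist and mask that person to group:

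- Supply study numbers only, in a testing order that mixes intervention, control and normative children.
- Withhold the allocation list and the game records until scoring is complete.
- Instruct community workers, ECD staff and families not to disclose a child's group.
- Record any unmasking when it happens, and report it by group.

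State this in the protocol. If masking is already in place, one sentence saying so and how it is protected would settle the point.

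The Abstract says all baseline assessments are done, so nothing is proposed for that round. Results is looser and says only that most recruitment was complete. If any child is still to be assessed at baseline, score that assessment before the allocation is released.

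The cost is a scheduling list, a short instruction and a line on a form, with no extra staff and no change to the intervention. The downside is that some children may disclose their group; the record of unmasking would show how often.
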